**Data collection**
Interviews will be conducted with individuals or in groups and arranged at a mutually convenient time and place, preferably at the participant’s place of work. The interview will be recorded using a digital sound recorder and will last 30–60 min.
**Data analysis**
The data will be analysed using framework analysis [43]. The framework will be informed by the theory of planned behaviour which has been used previously to explore dental practitioner’s clinical practice [44]. Two researchers will be involved in the analysis of the qualitative data.

C), D), and E)
***Evaluation of retention rates and completion rates, acceptability of the guided self-help CBT resource, evaluation of potential outcome measures, and sample size calculation***

**Design of the study**
This stage will comprise a pre-post test single group design and will involve asking a consecutive sample of young people and their parents to complete the resource to evaluate retention, completion rates, and acceptability, to evaluate potential outcome measures and provide data to allow a sample size calculation for an RCT. Participants will be asked to complete a battery of measures and will then be given the resource to work through with their parent or carer and clinician. After they have completed three visits for dental treatment, they will then complete the questionnaire a second time. The questionnaire will include patient demographic information, dental anxiety (Modified Child Dental Anxiety Scale [45]), and health-related quality of life (Child Health Utility 9D) [46]. A sample of young people and parents/carers will also be interviewed to explore the acceptability of the resource. The interviews will be digitally recorded and transcribed verbatim as quickly as possible after the event and the recordings deleted after a short time. All identifying information will be removed from the transcripts to ensure anonymity.
**Setting and recruitment**
The research participants will be recruited purposively from new patients to a general dental practice in South Yorkshire, Derbyshire, salaried dental service and the Paediatric Dentistry Department of the Charles Clifford Dental Hospital in Sheffield. The sample will be recruited to involve young people living in areas with a range of different levels of deprivation and from different black and ethnic minority groups. It is expected that a total of 100 families will be recruited.Identification: potential participants will be identified by their dentist based on the inclusion and exclusion criteria.Initial approach: potential participants and their parents will be approached by a research nurse and the young person will be asked ‘Do you feel worried or afraid about going to the dentist?’ If they say ‘yes’ then they will be invited to take part in the study.Recruitment: after the initial approach, the children and their parents will be given separate written information sheets to take away and read.At the next dental appointment, which is part of the child’s normal course of planned treatment and will typically involve a non-anxiety-provoking preventive treatment, child and parental consents will be obtained from those wishing to participate in the study. At this time, the CBT resource will be provided and the participant will also complete the baseline questionnaire (T_1_).The participant will continue along their normal care pathway for their course of treatment (which could include treatment under inhalation sedation) and will work through the CBT resource at subsequent visits with the same dentist. At their third visit, they will complete the same questionnaire again (T_2_) and continue with their course of treatment as normal. The time interval between T_1_ and T_2_ will vary between participants.

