**Data collection**
Data will be collected about the following outcomes: dental anxiety, health-related quality of life, acceptability, missed or cancelled appointments, completion of the course of treatment, and the level of engagement with the resource.A battery of outcome measures including the Modified Child Dental Anxiety Scale [36] and the Child Health Utility 9D [46] will be given to the participants to complete then the CBT resource will be introduced along with the accompanying instructions for young people and their parents. Interviews will be arranged once the participants have completed their course of dental treatment and as much of the resource as they want. Data will also be recorded by a member of the clinical care team to include: missed or cancelled appointments, completion of the course of treatment, and the level of engagement with the resource.The interviews will take place at a mutually convenient time and place, preferably at the young person’s home. The interview will be recorded using a digital sound recorder and will last for 45–60 min. Interviews will be conducted with both parents and children.

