**Data analysis**
The qualitative data will be analysed using framework analysis [43]. Two researchers will be involved in the analysis of the qualitative data. Quantitative data will be entered into an electronic database (Statistical Package for Social Sciences, v20) and analysed using simple descriptive statistics, internal consistency (Cronbach’s alpha) and validity through correlation coefficients to evaluate the performance of the measures. Our main outcomes of interest are take-up, recruitment rates, use of the resource, completion rates, and our ability to gather data at baseline and follow-up.

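### The feasibility cohort in parts C, D and E is called both consecutive and purposive; if individuals are chosen purposively, its take-up and recruitment rates would not represent all eligible patients.

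*Protocol article*

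**What the plan says.** All the text is in the protocol article, in the sections for parts C, D and E.

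- Design of the study: this stage "will involve asking a consecutive sample of young people and their parents to complete the resource to evaluate retention, completion rates, and acceptability". It is also to supply the data for the sample size of a later randomised trial.
- Setting and recruitment: "The research participants will be recruited purposively from new patients to a general dental practice in South Yorkshire", with further sources in Derbyshire, the salaried service and the dental hospital. The aim of the selection follows: "The sample will be recruited to involve young people living in areas with a range of different levels of deprivation", and from different ethnic groups. The target is then given: "It is expected that a total of 100 families will be recruited".
- The same section sets out a pathway. It starts with "potential participants will be identified by their dentist based on the inclusion and exclusion criteria". A research nurse then approaches the family and asks the child one question about worry, those who answer yes are invited, and consent is taken at the next appointment.
- Data analysis: "Our main outcomes of interest are take-up, recruitment rates, use of the resource, completion rates", with the ability to gather data at the two time points as the fifth.

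**The concern.** The two sampling terms give a site different instructions. Consecutive means that every eligible patient is approached in order of arrival. Purposive, applied to individuals, means that some eligible patients are passed over because the sample already has enough like them. For interviews that is sensible. For a rate it matters, because the patients passed over drop out of the figure.

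Take-up and recruitment rates are named first among the main outcomes, and the Discussion says the findings on recruitment will inform a future trial. If sites select individuals, the observed rates describe the families chosen to be approached and not the eligible patients a later trial would draw on. Retention and completion are measured in the same children, so how well they carry over depends on the same selection. The problem cannot be repaired afterwards, because the response of families who were never approached is not observed.

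**Working it through.** **1. Do both statements concern the same cohort?** Yes. The setting and recruitment section that says purposive goes on to the 100 families, the provision of the resource, and the questionnaires at T1 and T2. The interview group is mentioned separately in the design section as a further sample. The word purposive therefore cannot be confined to the interviews.

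**2. Is there a reconciling sentence?** No. Purposive choice of sites with consecutive patients inside each site would reconcile the two, but the text attaches the word to the participants and describes the spread in terms of young people.

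**3. Is the sample size affected?** Inputs from the sample size section: 60 wanted at follow-up, 40% drop-out.

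N = 60 / (1 − 0.40) = 60 / 0.60 = 100.

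This reproduces the plan's figure exactly and does not depend on the sampling method. Retention also keeps a clear denominator: if 60 of 100 are followed up it is 60%, Wilson 95% interval 50.2% to 69.1%.

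**4. Can take-up be calculated?** Yes, among those approached or invited, since the pathway has countable stages. The article gives no expected number invited, so the following numbers are assumptions. With 100 recruited:

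| Invited (assumed) | Take-up among invited |
|---|---|
| 120 | 100/120 = 83% |
| 150 | 100/150 = 67% |
| 200 | 100/200 = 50% |
| 300 | 100/300 = 33% |

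**5. How far could that rate lie from the rate among all eligible families?** Let f be the share of eligible families approached, 60% the take-up observed among them, and u the take-up that the others would have shown (all assumed). Then

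rate among all eligible = f × 0.60 + (1 − f) × u.

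| f | u = 20% | u = 40% | u = 60% |
|---|---|---|---|
| 1.00 (consecutive) | 60% | 60% | 60% |
| 0.75 | 50% | 55% | 60% |
| 0.50 | 40% | 50% | 60% |
| 0.25 | 30% | 45% | 60% |

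For f = 0.50 and u = 20%: 0.50 × 0.60 + 0.50 × 0.20 = 0.40, so the observed rate overstates by 0.60/0.40 = 1.5. At u = 60% the factor is 1.0. If u were above 60%, the observed rate would be too low. Only under consecutive recruitment (f = 1) does the answer not depend on u.

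**The case against.** The strongest reply is that the authors probably mean purposive sites and consecutive patients. In part B the same wording is tied to dental practices serving areas of differing deprivation, and in parts C, D and E the dentist identifies patients on the eligibility criteria. This is a plausible intention, and the fix below adopts it. It is not what the text says, however, and a site reading only the recruitment section could properly select individuals.

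Four stronger conclusions are tempting, and the document does not support them.

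- A reader might infer that the rates have no valid denominator. They do: the pathway gives countable stages, and the other three main outcomes (use of the resource, completion and data capture) can be taken over the recruited children.
- A reader might infer that the rates cannot be computed because the data collection section lists no counts of families approached or declining. That section begins "Data will be collected about the following outcomes: dental anxiety, health-related quality of life, acceptability, missed or cancelled appointments" and deals with participant-level data. A screening log is commonly left to the full protocol, which is not shown, so its absence from an article is no finding.
- A reader might infer that dentists will pick receptive families and so inflate the rate. The only stated basis for identification is eligibility, and selection for deprivation and ethnic mix could move the rate either way.
- A reader might infer that a later trial would need twice the sites or time. With half of eligible families approached, a factor of two requires that none of the others would accept (0.50 × 0.60 + 0.50 × 0 = 0.30). In the table above it appears only in the extreme cell, with a quarter approached and 20% acceptance among the rest.

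It is also fair to say that part A, a consecutive survey, is meant to help estimate how many patients must be assessed for a future trial, so recruitment planning does not rest on this cohort alone. Part A covers one hospital department, ages 11–16 and stated willingness. Parts C, D and E add ages 9–10, general practice and actual consent, so the point keeps its weight.

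**Conclusion.** The contradiction stands: one cohort, two incompatible descriptions, and nothing to reconcile them. Its direct effect is on the interpretation of two of the five main outcomes. Under purposive selection of individuals, take-up and recruitment rates describe those approached or invited, not all eligible patients, with a bias whose direction and size the document does not allow anyone to determine. The 40% to 60% range for an observed 60% rests wholly on the assumed half approached and 20% to 60% acceptance among the rest; it illustrates the uncertainty and does not estimate it. Retention and completion are affected only in how far they represent eligible patients. This should be fixed before recruitment, but it does not invalidate the study.

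**What to change.** In the setting and recruitment section for parts C, D and E, state that sites are chosen purposively for their deprivation and ethnic mix and that, within each site, every consecutive eligible new patient is approached until 100 are enrolled. This agrees with the design section and keeps the intended diversity. Reserve purposive selection of individuals for the interview subsample.

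In the data analysis section, report take-up in two forms: consented over eligible, and consented over approached. Under consecutive recruitment the two should be close, and a gap between them shows how many eligible families were missed.

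The cost is a few sentences, plus counts at stages the research nurse and dentists already carry out. The one real downside is less direct control over the deprivation and ethnic mix, which would then depend on the choice of sites.

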**Sample size**
For the qualitative aspect, no formal sample size calculation has been carried out although previous studies have required interviews with 10–15 participants before data saturation is reached [47, 48].In order to evaluate the potential outcome measures and determine the sample size for a future RCT, a total sample size of 60 participants will be sought. A sample size of 50 is recommended by Consensus-based Standards for the selection of health measurement instruments [49]. Allowing for a 40 % drop-out rate between baseline and follow-up, the intent is to recruit 100 participants.
**Type of participants**
The following inclusion and exclusion criteria will be adopted:
*Inclusion criteria*
Children aged 9–16 years old with mild to moderate dental anxietyChildren requiring a course of dental treatment which requires at least three separate visits

*Exclusion criteria*
Children diagnosed with an underlying psychological disorderChildren with an acute dental problem who require urgent dental treatmentChildren with a severe disability where communication is not possibleNon-English speaking children and parent/carers (to avoid the need for translating services where the participant’s responses might be unintentionally altered as a result of being translated)

**Data collection**
Data will be collected about the following outcomes: dental anxiety, health-related quality of life, acceptability, missed or cancelled appointments, completion of the course of treatment, and the level of engagement with the resource.A battery of outcome measures including the Modified Child Dental Anxiety Scale [36] and the Child Health Utility 9D [46] will be given to the participants to complete then the CBT resource will be introduced along with the accompanying instructions for young people and their parents. Interviews will be arranged once the participants have completed their course of dental treatment and as much of the resource as they want. Data will also be recorded by a member of the clinical care team to include: missed or cancelled appointments, completion of the course of treatment, and the level of engagement with the resource.The interviews will take place at a mutually convenient time and place, preferably at the young person’s home. The interview will be recorded using a digital sound recorder and will last for 45–60 min. Interviews will be conducted with both parents and children.
**Data analysis**
The qualitative data will be analysed using framework analysis [43]. Two researchers will be involved in the analysis of the qualitative data. Quantitative data will be entered into an electronic database (Statistical Package for Social Sciences, v20) and analysed using simple descriptive statistics, internal consistency (Cronbach’s alpha) and validity through correlation coefficients to evaluate the performance of the measures. Our main outcomes of interest are take-up, recruitment rates, use of the resource, completion rates, and our ability to gather data at baseline and follow-up.

## Discussion

This study protocol is designed to investigate the feasibility of evaluating, in an RCT, a CBT resource for young people (9–16 years) for the reduction of dental anxiety. The findings will provide valuable information regarding recruitment (including sample size), the most appropriate outcome measures, retention and completion rates, and the acceptability of the guided self-help CBT resource to patients, parents, and clinicians informing the design of a future RCT. If in a subsequent RCT the guided self-help CBT resource is found to be effective at reducing dental anxiety, these findings would be relevant to both users (young people and their parents) and service providers (dental practitioners and NHS).

One key issue to consider throughout this study is the involvement of children and young people themselves in the development, modification, and evaluation of the resource. Involving children throughout the research process is important as they have their own perspectives and these should be taken onto account whilst making decisions about their care [50]. A recent systematic review suggested the need for greater child-centred oral health research especially for evaluating the effectiveness of clinical interventions which could have a positive impact on the health outcomes for children and young people [51]. Additionally, engaging children in research enables age-appropriate measures to be chosen, ensures sustainable recruitment strategies, and assists in better dissemination [41, 52].

In terms of participant comfort, it is not anticipated that participants will feel distressed during the course of the study. However, discussing dental anxiety could lead a participant to consider a traumatic past dental experience and its impact. If a participant does become upset, the interview will be stopped until the participant feels able to continue. The researcher conducting the interviews will have the appropriate training and experience to support young people who have suffered unfavourable dental experiences. If through involvement in the study a participant is identified as having an undiagnosed psychological disorder, this will be dealt with by the clinical dental teams and a referral will be made to the Child Adolescent Mental Health Service.

Practical issues involved in performing the study will be challenges of involving general dental practices in research. These include ensuring early and continued involvement of clinic staff in the research study, developing the research capacity within the dental practice, e.g. training in research methodology, and maintaining enthusiasm for the research to ensure progress and momentum of the study [53].

The study findings will be widely disseminated through presentations at national and international dental and psychotherapy conferences and publications in peer-reviewed journals. A wider programme of dissemination will involve patients and the public. The findings will be disseminated back to participating young people and their parents in an easy read report. The findings will also be posted on the ‘dental fear in children’ thread of the Dental Fear Central forum, an international online resource for those with dental anxiety and dental professionals. A project steering group will be convened to include two members of the Sheffield Health watch and a parent representative as well as the research team and collaborators. The project steering group will meet every 6 months during the project. A panel of five young people (aged 11–16 years) will also be assembled and will meet twice during the project. The project steering group and young people’s panel will be involved in designing participant information leaflets, consent forms, questionnaires, and the topic guides for the qualitative interviews. The steering group and panel will also discuss and help interpret the results of the study, advise on dissemination, and make recommendations for the design of the pilot trial to evaluate the effectiveness of the resultant CBT resource.

## Abbreviations

CBT: cognitive behavioural therapy
NHS: National Health Service
RCT: randomised control trial
